#### Intervention processes and mechanisms (Aim 3)

To test theory-based, therapeutic ACT processes and mediators in *REVITALIZE*, we use the *Experiences Questionnaire-Decentering* scale [60] to assess cognitive defusion and acceptance, and the *Valuing Questionnaire* [61] to assess aligning behavior with personal values.

### Data analytic approach

The statistical analysis will be conducted according to the intention-to-treat principle, with all randomized participants included in the primary analyses. Descriptive statistics will be used to evaluate baseline and follow-up outcome measures, including assessment of distributions, potential outliers, and patterns of missing data. For continuous outcomes, we will summarize mean changes from baseline with corresponding 95% confidence intervals (CIs) at each follow-up time point for both groups (Enhanced Usual Care vs. *REVITALIZE*). For binary outcomes (e.g., presence of PARP inhibitor dose delays, interruptions, or discontinuation), we will estimate proportions with corresponding 95% CIs. If clinically meaningful imbalances are observed between groups, adjusted analyses using regression or stratified models will be performed.

For Aim 1, the primary analysis of change in fatigue interference at week 20 will tested using a a two-sample t test (without covariate adjustment). As a secondary analysis, linear regression (ANCOVA) of the outcome on the intervention indicator, adjusting for the baseline value of the outcome and prespecified baseline variables (race/ethnicity, education, age, and income) will be used. If any baseline variable shows imbalance (standardized mean difference > 0.10), it will be retained in the regression model; otherwise only the baseline value of the outcome will be included alongside the variable for condition. Longitudinal mixed-effects models will be conducted as additional secondary and sensitivity analyses. Aim 2 adherence outcomes will be assessed using mixed-effects models for Wisepill data and logistic regression for binary adherence indicators. Aim 3 will evaluate whether the conditions differ on change over time in the hypothesized process variables for *REVITALIZE—* acceptance and values alignment. In addition, we will test mediation of intervention effects on fatigue interference through acceptance and values alignment using the linear regression mediation framework outlined below as well as the multiple mediation framework of Preacher and Hayes [62], with sensitivity analyses using structural equation models.

Data transformations or non-parametric approaches will be considered if model assumptions are not satisfied. Sensitivity analyses will be conducted in the per-protocol population, and all results will be reported in accordance with CONSORT guidelines. Regarding missing data, we will compare baseline characteristics of patients with complete follow-up to those without by randomized condition to assess potential biases in the complete case analysis. We will conduct sensitivity analyses using all available case analysis (among the subset of participants with complete data at baseline and one post-baseline point) as well as additional methods such as multiple imputations by chained equations.

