At the primary community site of RMCC, we will use the triple strategy of practitioner referrals and outreach to potentially eligible patients, direct patient mailings, and onsite flyers—approaches we have used successfully in previous trials with RMCC [25, 35–38]. If needed, we will send an RA onsite to a large RMCC clinic to recruit, a strategy we have piloted but only use as a back-up strategy due to its time and resource demands. Once a potential participant contacts the study team for more information or is referred by a provider, the University of Colorado research team will contact them to share study details and, if interested, complete study eligibility screening. If the person is eligible and interested, the study’s oral informed consent process is initiated with consent documented using REDCap’s e-consent framework. After completion, participants are sent a copy, asked to complete a baseline survey, and provided with a wireless pillbox.

The consent form includes that study participation is entirely voluntary, that participants’ clinical care will not be compromised in any way if they withdraw from the study, and that participants can be removed at the discretion of the principal investigators ([name] and [name]) for reasons such as violating reasonable expectations for study participation.

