### Power and sample size estimation

We plan to enroll a total of 240 patients (approximately 120 per condition) in the study. Based on findings from the *REVITALIZE* pilot study and our recent RCT for adults with advanced cancer [25], we anticipate 20% missing data at 20-week FU. Accordingly, we expect data from 192 patients (*n* = 96 per group) to be available for the primary analysis of the primary endpoints for each Aim.

For Aim 1, the primary analysis will use a two-sample t-test. With a sample size of 192, the study will have 80% power to detect a significant intervention effect corresponding to Cohen’s d = 0.41 (a small-to-moderate effect size) at a two-sided alpha level of 0.05, and 94% power to detect a moderate effect size (d = 0.50). These thresholds are smaller than the effect sizes observed in the pilot trial [27], where the primary endpoint yielded approximately an effect size of d = 0.94 for the *REVITALIZE* intervention group versus EUC at follow-up, and the targeted secondary endpoints yielded effect sizes of d≥0.60. Thus, the planned sample size provides sufficient power to detect clinically meaningful effects for Aim 1.

For Aim 2, the primary analysis for chart review data will use Fisher’s exact test. With a sample size of 192, the study will have 80% power to detect an intervention effect corresponding to Cohen’s h = 0.4 (a small-to-medium effect size) at a two-sided alpha level of 0.05, and 93% power to detect a moderate effect size (h = 0.5). The longitudinal outcomes, assessed using monthly Wisepill adherence data, provide even greater statistical power than the chart review outcomes because they involve repeated continuous (rather than single binary) measurements. Accordingly, we consider the study to be adequately powered for the outcomes specified in Aim 2 [63].

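### The article promises that all randomised participants enter the primary analyses, but the Aim 1 primary test is a complete-case t-test expected to use about 192 of 240

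*Protocol article*

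**What the plan says.** All references are to the protocol article.

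- *Data analytic approach*, first paragraph: analysis follows intention-to-treat, "with all randomized participants included in the primary analyses".
- *Data analytic approach*, second paragraph: change in fatigue interference at week 20 is tested by a "two-sample t test (without covariate adjustment". ANCOVA is a secondary analysis, and longitudinal mixed models are secondary and sensitivity analyses. No imputation is attached to the primary test.
- *Data analytic approach*, last paragraph: baseline characteristics of participants with and without complete follow-up will be compared by condition "to assess potential biases in the complete case analysis". An all-available-case analysis and multiple imputation by chained equations follow as sensitivity analyses.
- *Power and sample size estimation*: "We plan to enroll a total of 240 patients (approximately 120 per condition) in the study"; "we anticipate 20% missing data at 20-week FU"; hence 192 participants, 96 per group, are expected "to be available for the primary analysis of the primary endpoints for each Aim".
- *Study timeline* and Table 1: patient-reported outcomes are collected at baseline and weeks 8, 13, 20 and 28. Completing the baseline survey is an inclusion criterion and comes before randomisation.
- *Measures*: participants who leave the intervention, or who progress but wish to stay in the study, may go on completing assessments.

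**The concern.** A change score at week 20 exists only for someone with a week-20 value. A t-test on that score, with nothing imputed, leaves out everyone else. The article therefore gives its primary analysis a property, inclusion of all randomised participants, that the specified test does not have. A reader of the results could take the headline estimate to apply to everyone randomised when it applies to completers.

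This matters because randomisation protects the comparison of everyone randomised, not of those who return a survey some five months after baseline. The outcome is self-reported. One arm is asked to attend up to ten sessions with home practice, while the other receives a book and usual care. Missingness could depend on outcome and could differ between arms. Enlarging the sample to 240 protects power against a 20% loss; it does not protect against that kind of selection.

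**Working it through.** **1. Reproduce the plan's own figures.** Inputs from *Power and sample size estimation*: 240 randomised 1:1, 20% missing, two-sided alpha 0.05, two-sample t-test.

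- Analysed number: 240 × (1 − 0.20) = 192, or 96 per arm. This matches, and 240 − 192 = 48 randomised participants are outside the primary test.
- Power at 96 per arm (noncentral t, noncentrality d / √(1/96 + 1/96)): 80.7% at d = 0.41 (stated 80%) and 93.1% at d = 0.50 (stated 94%). The effect detectable with 80% power is 0.406. The stated figures reproduce within rounding tolerance.
- Power at 120 per arm: 88.6% at d = 0.41 and 97.1% at d = 0.50, with a detectable effect of 0.363. The stated power is therefore that of a test on 192 completers, not on all 240.

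The figures at 120 per arm are a ceiling on what recovering the missing values could add to the unadjusted comparison, since a mixed model or imputation recovers only part of that information.

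**2. Set the statements side by side.** The population statement implies 240. The test as specified, the complete-case wording and the power basis all imply about 192. Every method that could bring in the other 48 is ranked below the primary test.

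**3. Illustrate what could follow.** The inputs below are assumptions except the 20% and d = 0.41.

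*Effect over all randomised*, with a fraction m missing in each arm: d_all = (1 − m) × d_completers + m × d_missing. With m = 0.20 and d_completers = 0.41:

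| Effect in the missing | Effect over all randomised |
|---|---|
| 0.41 | 0.41 |
| 0 | 0.8 × 0.41 = 0.328 |
| −0.41 | 0.328 − 0.082 = 0.246 |

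In the middle row the completer estimate exceeds the all-randomised effect by 0.41 / 0.328 − 1 = 25%.

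*Bias when there is no true effect.* Suppose missing participants do k SD worse than completers in their own arm. The completer mean is then shifted favourably by m × k, so the bias in the arm difference is (m_REVITALIZE − m_EUC) × k, in favour of REVITALIZE when that arm loses more:

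| Missing, REVITALIZE / EUC | k = 0.5: bias, type I error | k = 1.0: bias, type I error |
|---|---|---|
| 20% / 20% | 0; 5.0% | 0; 5.0% |
| 25% / 15% | 0.10 × 0.5 = 0.05 SD; 6.4% | 0.10 SD; 10.6% |
| 30% / 10% | 0.20 × 0.5 = 0.10 SD; 10.5% | 0.20 SD; 27.7% |

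Type I error is the two-sided rejection rate of the nominal 5% t-test with 120 × (1 − m) participants in each arm. With equal missingness and equal mechanisms the bias is zero. The article gives neither missingness by arm nor the outcomes of those missing, so it does not say which row applies.

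**The case against.** The strongest reply is that this is a conflict of wording in a plan that otherwise treats missing data with care. The 20% loss is foreseen and built into the sample size. Completers and non-completers will be compared by arm. Mixed models, an all-available-case analysis and multiple imputation are all planned, so data from weeks 8, 13 and 28 are not discarded. One sentence could align the population statement with the test, and choosing a mixed model as primary is a choice among defensible methods. It also assumes missing at random: if non-completers get no benefit in a way that earlier visits do not reveal, it would not recover 0.33 in the illustration above.

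Much of this stands. The planned analyses soften the consequence, and the limit of the mixed model is real. They do not remove the contradiction, because none of them is primary. Nor is this detail that an article may leave to the analysis plan: the article itself fixes the test, the analysed number and the rank of each missing-data method.

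Three stronger readings are tempting and lack support.

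- *Progression drives dropout.* The article does not say so. It bases the 20% on the pilot and an earlier trial, gives no reasons for the losses, and lets participants who progress go on completing assessments. Progression is one possible route to informative missingness, no more.
- *Removal by investigators depletes one arm.* *Participant recruitment and consent* says that "participants can be removed at the discretion of the principal investigators". It does not say that removal ends the surveys or takes anyone out of the analysis set, nor that it would fall mainly on one arm; both arms have surveys and a pillbox.
- *The trial is underpowered.* It is not, on its own terms: the calculation already uses 96 per arm.

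**Conclusion.** The statement that all randomised participants are included in the primary analyses is wrong as written for Aim 1. The primary test is complete case and is expected to omit 48 of 240 (20%), so its estimate would be for completers. This rests only on the article's own text and figures.

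Whether the estimate would also be biased, and by how much, depends on facts the article does not give. Under the assumptions shown, the consequence runs from none (equal missingness and equal mechanisms), through 0.05 SD with a type I error of about 6.4% (25% versus 15% missing, 0.5 SD worse), to a completer effect of 0.41 standing for 0.33 over all randomised (no benefit in the missing 20%). These are illustrations, not forecasts.

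**What to change.** **Preferred.** Make the already planned longitudinal model the Aim 1 primary analysis. Fit it by likelihood, with interference at baseline and weeks 8, 13, 20 and 28 in the outcome vector, arm-by-visit terms and the stratification factors, and take the week-20 contrast between arms as the primary result. Baseline is complete for everyone randomised, so placing it in the outcome vector lets all randomised participants contribute. Keep the complete-case t-test as a sensitivity analysis. Because the model assumes missing at random, add a delta-adjusted version of the planned multiple imputation in which missing REVITALIZE values are made progressively worse.

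**Minimum.** If the t-test stays primary, replace the population sentence: participants are analysed in the arm to which they were randomised, whatever their attendance, and the primary test uses those with baseline and week-20 data.

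**Cost.** No new data are needed, since the visits, the mixed model and the imputation are already planned. The preferred route requires the primary method and its power basis to be restated and a protocol modification to be approved before any unblinded analysis, plus some extra programming. The minimum route changes one sentence, but leaves the headline result a completer estimate.

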## Methods/design

### Study design and funding

This study is a two-arm, prospective RCT that aims to randomize 240 patients with advanced ovarian cancer who are currently prescribed PARP inhibitors and report moderate to severe fatigue. Participants are individually randomized 1:1 to either *REVITALIZE* or EUC based on a randomization block sequence generated by the study biostatistician ([name]) using R statistical software [31], stratified by PARP inhibitor type and regimen (once versus twice daily and with versus without bevacizumab) and recruitment site. Patient-reported outcomes will be collected in Research Electronic Data Capture (REDCap) [32], a HIPAA-approved, secure, web-based tool, at five timepoints: baseline (pre-intervention), mid-intervention (8 weeks after baseline), post-intervention (13 weeks after baseline), and 20- and 28-week follow-ups (FU). The 20-week FU serves as the main endpoint, and the 28-week FU serves to assess maintenance or change in effects over time. Adherence outcomes will be assessed via Wisepill, a wireless adherence tracking device [33] and medical chart review.

The study was pre-registered with identifier NCT06710548 on Clinicaltrials.gov on November 29, 2024, before enrolling the first patient (https://clinicaltrials.gov/study/NCT06710548). Dana-Farber Cancer Institute serves as the single IRB overseeing the study and informed consent is obtained from all individuals prior to study enrollment.

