### Study eligibility criteria

#### Inclusion criteria

Adult (age ≥18 years), English-speaking patients with advanced ovarian cancer will be eligible to participate if they:

Have epithelial ovarian cancer (including ovarian, fallopian tube, and primary peritoneal cancers, all of which are treated as ovarian cancers).Are being treated with PARP inhibitors as a maintenance therapy after completion of first-line treatment or platinum-sensitive recurrent disease, and have taken the PARP inhibitors for at least 2 months. This corresponds to the time period when patients frequently undergo dose reductions, delays due to symptoms and side effects, and switches to other PARP inhibitors. After 2 months, most patients are on a stable dose that can be continued for the duration of their treatment.Anticipate continued treatment on a PARP inhibitor for at least 8 months at time of consent (e.g., beyond the duration of the study).Report an average rating of ≥ 4 (range 0–10) on the first 3 items of the Fatigue Symptom Inventory [28, 29], which rates fatigue levels during the past week on the most and least fatiguing day and on an average day. We used this same cutoff score in the REVITALIZE pilot study [27].Report a rating of 0 to 2 on the Eastern Cooperative Oncology Group Performance Status Scale (ECOG) performance status at time of consent [34], indicating that they are out of bed most of the day.Are capable at time of consent of understanding and voluntarily consenting to the study, attending online sessions, and completing homework for the intervention, which includes engaging in valued activities. Also, are willing to use a wireless electronic pillbox for PARP inhibitor medication.Complete the baseline (pre-intervention) survey.

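### The primary t test on change is valid but leaves precision unused; a fixed-term ANCOVA on baseline and the randomization factors would be the better primary analysis

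*Protocol article*

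**What the plan says.** Under Data analytic approach, the week-20 change in fatigue interference "will tested using a a two-sample t test (without covariate adjustment"). Power and sample size estimation repeats the choice: "For Aim 1, the primary analysis will use a two-sample t-test".

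The same analysis section lists ANCOVA as a secondary analysis, "adjusting for the baseline value of the outcome and prespecified baseline variables (race/ethnicity, education, age, and income"). The listed covariates then face a data-dependent rule: "If any baseline variable shows imbalance (standardized mean difference > 0.10), it will be retained in the regression model". Without such imbalance, only the baseline outcome value stays in the model with arm. Mixed models are further secondary and sensitivity analyses.

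Two facts about the design bear on this:

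- Inclusion criteria require that participants "Complete the baseline (pre-intervention) survey", and Study timeline puts that survey before randomization. The baseline covariate therefore exists for everyone randomized.
- Study design and funding describes 1:1 randomization "stratified by PARP inhibitor type and regimen (once versus twice daily and with versus without bevacizumab) and recruitment site". These factors appear neither in the primary test nor in the covariates named for the ANCOVA.

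The article gives no reason for preferring the unadjusted test.

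**The concern.** A t test on change is a regression in which the coefficient of baseline is set to 1. ANCOVA estimates that coefficient. Three consequences follow for the headline result.

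- **Precision.** Residual variance under the change score is at least as large as under ANCOVA, so the primary test can have less power than the same data allow.
- **Chance imbalance.** When the true baseline slope is below 1, subtracting the whole baseline value over-corrects a chance difference between arms and shifts the estimate.
- **Strata.** If the stratification factors predict outcome, a test that ignores them uses a standard error that is somewhat too large.

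All three concern the single primary test. The baseline-adjusted model is already planned, so the question is mainly which analysis carries the primary label, and with which terms.

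**Working it through.** **Inputs from the Protocol article.** Allocation is 1:1. The plan is "We plan to enroll a total of 240 patients (approximately 120 per condition) in the study", with 20% missing at week 20, so 240 × 0.8 = 192 analysed, 96 per arm. Two-sided alpha is 0.05. Stated power is 80% at d = 0.41 and 94% at d = 0.50.

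**Reproducing the stated power.** The noncentrality is d × √(n/2) = d × √48, on 190 df.

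- d = 0.41: 80.7% (stated 80%).
- d = 0.50: 93.1% (stated 94%).

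Both agree to within a point. There is no error in the power statement.

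**Variance comparison.** Let s0 and s1 be the baseline and week-20 SDs, r their correlation and k = s0/s1.

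- Var(change) = s0² + s1² − 2·r·s0·s1
- Var(ANCOVA) = s1²(1 − r²)
- Difference = (s0 − r·s1)², which is never negative
- Ratio ANCOVA/change = (1 − r²)/(1 + k² − 2rk), which reduces to (1 + r)/2 when k = 1

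The direction therefore needs no assumption about r or k. The size needs both, and the document gives neither.

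**Power with baseline in the model.** The assumptions are r = 0.3 to 0.7 and k = 1 or 0.8, with d = 0.41 in change-score SD units and 96 per arm. Power uses 189 df and a small-sample inflation of 1 + 1/188 for one estimated covariate. Example for r = 0.5, k = 0.8: ratio 0.75/0.84 = 0.893; inflated 0.898; effective d = 0.41/√0.898 = 0.433; power 85%.

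| r | Ratio, k = 1 | Power | Ratio, k = 0.8 | Power |
|---|---|---|---|---|
| 0.3 | 0.65 (35% less) | 94% | 0.784 (22% less) | 89% |
| 0.5 | 0.75 (25% less) | 90% | 0.893 (11% less) | 85% |
| 0.7 | 0.85 (15% less) | 86% | 0.981 (2% less) | 81% |

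The comparator throughout is 80.7%. A k below 1 is plausible because entry requires an average of at least 4 on the first three FSI items, which may narrow the baseline spread of interference. At k = 1.2 the powers would be 97%, 95% and 93%. At k = 0.7 and r = 0.7 the baseline slope r/k is exactly 1 and the gain vanishes.

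**Simulation check** (10,000 replicates per scenario, k = 1, r = 0.3, 0.5, 0.7). Type I error was 4.7%, 5.0%, 4.9% for ANCOVA and 4.9%, 5.1%, 4.8% for the t test. Power was 93.8%, 90.4%, 86.3% against 81.0%, 80.6%, 80.7%.

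**Chance imbalance.** The baseline slope is r/k, which is below 1 in every cell of the table, so the change score over-corrects. At r = 0.5 and k = 1, a 0.2 SD baseline difference moves the estimate by (1 − 0.5) × 0.2 = 0.1 SD. The change SD there is √(2(1 − 0.5)) = 1, so this is 0.1/0.41, about a quarter of the target effect. With 96 per arm, a difference of at least 0.2 SD in either direction has z = 0.2/√(2/96) = 1.39, a chance of about 17%.

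**Cost of stratum terms.** Suppose 8 to 12 stratum terms (an assumed count) explain nothing. The inflation becomes 1 + 9/180 to 1 + 13/176. At r = 0.5 power is then 88–89% for k = 1 and 82–83% for k = 0.8. At r = 0.7 and k = 0.8 it is 79–80%, slightly below the t test. With equal SDs, break-even is at r of about 0.86–0.90 with these terms, and about 0.99 with baseline alone.

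**The retention rule.** For a continuous covariate and 96 per arm, P(|SMD| > 0.10) = P(|z| > 0.1/√(2/96)) ≈ 49% by chance (44% with 120 per arm). For at least one of four independent covariates it is 93% (90%). The terms of the existing ANCOVA would therefore be largely chosen by chance.

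**The case against.** The strongest reply is that nothing is wrong. The unadjusted t test is valid under 1:1 randomization, is stated consistently in both sections, and is the test on which the trial was sized. Ignoring prognostic strata is conservative and does not create false positives. A baseline-adjusted estimate will be reported anyway. At d = 0.50 the t test already has 93% power, and at the pilot effect of d = 0.94 more than 99.9%, so the gain matters mainly near the minimum detectable effect. All of this stands, and it limits the point to a recommendation.

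Three stronger readings are tempting and are not supported:

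- *That the trial is underpowered or its power statement wrong.* The stated figures reproduce.
- *That chance baseline imbalance is left uncorrected.* The endpoint is change, so baseline is subtracted. The accurate criticism is over-correction when the slope is below 1.
- *That variance falls by 35%, 25% or 15%, or that the gain at r = 0.5 is worth 256 analysed patients instead of 192 (192/0.75).* These figures require equal SDs, which the document does not give. At k = 0.8 the savings are 22%, 11% and 2%.

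Nor is the change wholly free. The baseline term costs one degree of freedom, but uninformative stratum terms cost a little more.

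**Conclusion.** The concern holds as a recommended improvement, not a must-fix. The primary test is sound, but it gives up precision that the trial has already paid to collect. That the change score cannot have the smaller residual variance follows from algebra. The size is an assumption: across r = 0.3 to 0.7 and k = 0.8 to 1, adjusting for baseline at d = 0.41 raises power from about 81% to between 81% and 94%, a gain of roughly 0 to 13 points. Any further gain from the randomization factors depends on how prognostic they are, which the document does not say. The existing secondary ANCOVA should not simply be promoted, because its covariates depend on the observed imbalance and it does not name the stratification factors.

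**What to change.** Make the primary analysis a linear model of week-20 fatigue interference with terms fixed in advance:

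- arm;
- baseline fatigue interference;
- the randomization factors (PARP inhibitor type and regimen, including bevacizumab, and recruitment site), with a prespecified rule for pooling small sites that states its threshold.

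Do not carry over the rule that retains covariates when the SMD exceeds 0.10. Keep the unadjusted t test on change as a sensitivity analysis. Leave the sample-size statement as it is, described as a conservative figure based on the unadjusted test.

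The cost is a wording change in the protocol and analysis plan, with a registry update, made before unblinding. No new data or patients are needed. The statistical downside is one degree of freedom for baseline and a small loss if the stratum terms turn out to be uninformative.

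### In the secondary ANCOVA, four demographic covariates called prespecified are kept only if their observed standardised difference exceeds 0.10, a threshold chance alone crosses 44% to 49% of the time

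*Protocol article*

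**What the plan says.** All of the relevant text is in the protocol article, Data analytic approach. The primary analysis of change in fatigue interference at week 20 is a t test with no covariates. The ANCOVA comes next: "As a secondary analysis, linear regression (ANCOVA) of the outcome on the intervention indicator", adjusted for the baseline value of the outcome and for four demographic variables, introduced as "prespecified baseline variables (race/ethnicity, education, age, and income) will be used".

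The following sentence makes those four conditional: "If any baseline variable shows imbalance (standardized mean difference > 0.10), it will be retained in the regression model". Where the threshold is not crossed, the plan falls back on a smaller model: "otherwise only the baseline value of the outcome will be included alongside the variable for condition". The paragraph before it contains a looser rule with no threshold, variable list or model: "If clinically meaningful imbalances are observed between groups, adjusted analyses using regression or stratified models will be performed".

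Under Study design and funding, randomisation is 1:1 and stratified by PARP inhibitor type and regimen and by recruitment site. None of the four demographic covariates is a stratification factor, so the design does not force balance on them.

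**The concern.** The two sentences on the ANCOVA pull against each other. The first lists the covariates in advance; the second lets the observed arms decide which of them stay. Among randomised participants a baseline difference is a chance event and says nothing about whether the variable predicts fatigue interference. The rule can drop a prognostic covariate because it happens to be balanced and keep a non-prognostic one because it is not.

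At stake is the one regression meant to gain from adjustment. Its covariate set would be unknown until the arms are compared, it would forgo precision in some realisations, and its nominal interval would take no account of the selection.

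**Working it through.** **Inputs.** From Power and sample size estimation: "We plan to enroll a total of 240 patients (approximately 120 per condition) in the study", and "we anticipate 20% missing data at 20-week FU". This leaves 192 analysed, 96 per arm. The threshold of 0.10 and the four candidates come from Data analytic approach.

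**The plan's own figures.** 192 / (1 − 0.20) = 240, as stated. At 96 per arm and two-sided 0.05, a t test has 80.7% power at d = 0.41 and 93.1% at d = 0.50 (normal approximation 81.1% and 93.4%). The plan states 80% and 94%, so its sample sizes can be used as they stand. It gives no figure for how often 0.10 is crossed by chance.

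**One covariate.** With n per arm, the observed standardised difference under randomisation is approximately normal with mean 0 and SE = √(2/n). The chance of crossing is P = 2 × [1 − Φ(0.10/SE)].

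| n per arm | SE | 0.10/SE | P |
|---|---|---|---|
| 120 | 0.129 | 0.77 | 43.9% |
| 96 | 0.144 | 0.69 | 48.8% |

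Simulation agrees: 43.9% and 49.0% for a continuous covariate, and 44–48% and 48–52% for a binary one with prevalence 0.1 to 0.5.

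**Four covariates, assumed independent.** At least one crosses with probability 1 − (1 − P)⁴: 90% at 120 per arm and 93% at 96. If each is kept or dropped separately there are 2⁴ = 16 possible models. At 96 per arm the binomial chances of keeping 0, 1, 2, 3 or 4 are about 7%, 26%, 37%, 24% and 6%.

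**Sensitivity to reading and coding.**
- If a categorical variable is screened with one multi-category difference, (n/2) × SMD² is approximately chi-square on k − 1 degrees of freedom. With an assumed k of 3 to 5 levels, the chance is 74–96% at 120 per arm and 79–98% at 96.
- If the difference were read as signed, the chance would be 22% or 24%. A rule about imbalance implies the absolute value.

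**Effect on the test.** A simulation (4,000 trials per setting, 96 per arm, no treatment effect) assumed a baseline outcome correlated 0.5 with the final outcome and four independent covariates.

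| Correlation of each covariate with outcome | Type I error, threshold rule | Type I error, all four fixed |
|---|---|---|
| 0.1 | 4.3% | 4.4% |
| 0.2 | 4.1% | 5.3% |
| 0.3 | 2.2% | 4.9% |

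The Monte Carlo SE is about √(0.05 × 0.95/4000) = 0.3 points, so the first row shows no difference. The baseline outcome leaves 1 − 0.25 = 0.75 of the variance. The four covariates together explain 0.04/0.75 = 5%, 0.16/0.75 = 21% and 0.36/0.75 = 48% of that, so the last row assumes strongly prognostic demographics. The direction makes sense: a balanced covariate left out adds little error to the estimate, but its variance stays in the residual and widens the interval.

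**Precision.** If the four explain a fraction r of the variance left after the baseline outcome, dropping all four multiplies the SE by 1/√(1 − r). For assumed r = 0.04 this is 1.02; for r = 0.16 it is 1.09. The documents give no value for r.

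**The case against.** The strongest defence is that this is a secondary analysis with a mechanical rule. The threshold is numeric, the candidates are named, and the rule uses baseline data and allocation but not outcomes. It leaves little room to choose a model for its treatment effect. That stands: the algorithm is prespecified, though the model it yields is not.

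Several stronger readings are tempting, and the text does not support them.
- A reader might infer that the trial's main conclusion is exposed. It is not, because the primary t test has no covariates.
- A reader might infer inflated type I error. The simulation shows the opposite direction.
- A reader might take the rule to open the list beyond the four variables. The preceding sentence names the four, and a term can only be retained if it was already proposed.
- A reader might conclude that the randomisation factors are absent from every model. The stated ANCOVA does exclude them, because its fallback admits only the baseline outcome and condition. Their place in the mixed models may be settled in an analysis plan not shown here.

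Two cautions on size also stand. The 90–93% figure assumes independence, and correlation among education, income, age and race/ethnicity would lower it. Balance is ordinarily checked on everyone randomised, which makes 44% the more natural single figure. Imbalance among completers could also reflect attrition, but fixed prognostic covariates deal with that better than a screen does.

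**Conclusion.** The point holds for the demographic terms of the secondary ANCOVA and no further. Each term is kept or dropped on something close to a coin toss: 44% on the randomised sample, 49% on the expected analysed sample, and more if a categorical variable is screened as a whole. These figures assume 1:1 randomisation, an absolute difference and, for the analysed sample, missingness unrelated to arm and covariate.

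The harm is modest and depends on prognostic strength, which the documents do not give. If the four covariates add little beyond the baseline outcome, almost nothing is lost. If they matter, precision is forgone and the test becomes conservative. It is worth correcting because the rule is stated outright, contradicts the label given to the covariates and is easily replaced.

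The looser sentence on clinically meaningful imbalances is a lesser matter. It adds a further data-driven route to adjusted results but does not displace the primary test.

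**What to change.** Delete the 0.10 rule and its fallback. State one ANCOVA covariate set now, chosen on prognostic grounds and included whatever the observed balance: the baseline outcome, those of the four demographic variables believed prognostic and, preferably, the randomisation factors with small sites pooled. Keep the sentence on clinically meaningful imbalances only if analyses prompted by it are labelled supportive.

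The cost is a text edit, with no change to design, conduct or sample size. The model uses roughly 5 to 15 or more degrees of freedom out of about 192 participants. The upper end arises if site is not pooled (Participant recruitment and consent lists five academic centres, a community network and affiliated regional practices, so about 6 degrees of freedom if coded as seven levels) and if race/ethnicity, education and income enter as several categories each.
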